**Cardiac Toxicity**

LVEF and clinical manifestations of cardiac function should be monitored during the administration of KN026. In the event of cardiotoxicity, treatment will be performed according to Table 6.

**Table6 Management of Cardiotoxicity of KN026**

| Severity                                                                                                                                          | Management                                                                                                                                                                                                    |
|---------------------------------------------------------------------------------------------------------------------------------------------------|---------------------------------------------------------------------------------------------------------------------------------------------------------------------------------------------------------------|
| Symptomatic left ventricular systolic dysfunction                                                                                                 | Permanent discontinuation                                                                                                                                                                                     |
| Decrease in LVEF (LVEF < 45% and $\geq$ 10% absolute decrease from baseline; or $\geq$ 15% absolute decrease from baseline) for more than 9 weeks | Permanent discontinuation                                                                                                                                                                                     |
| $\geq$ 15% absolute decrease in LVEF from baseline                                                                                                | Hold dose; repeat LVEF every 3 weeks: 
 
Resume KN026 if LVEF <math>\geq</math> 50% or LVEF <math>\geq</math> 45% and < 10% absolute decrease from baseline
 
 |
| LVEF < 45% and $\geq$ 10% absolute decrease from baseline                                                                                         | Hold dose; repeat LVEF every 3 weeks: 
 
Resume KN026 if LVEF <math>\geq</math> 50% or LVEF <math>\geq</math> 45% and < 10% absolute decrease from baseline
 
 |

***Tumor Lysis Syndrome***

KN026 and KN046 have the potential to cause ADCC effects and therefore are at risk for tumor lysis syndrome. Once it occurs, management may be performed according to Figure 3.

**Figure 3 Evaluation and Initial Treatment of Tumor Lysis Syndrome**

[figure not shown]

Note: Howard et al, 2011; TLS: tumor lysis syndrome

## **7 STUDY PROCEDURES AND EVALUATIONS**

### **STUDY VISIT PLAN**

The evaluation plan for this study is detailed in Table 1.

#### **Screening Period**

Subjects should sign the ICF before screening and the start of study evaluation. The screening period of this study is within 28 days prior to the administration of the study drug.

Subject information, including demographic information (date of birth, sex, and race) and complete medical history (including tumor history, prior and concomitant medications, prior surgery and radiotherapy, and baseline medical condition, etc.) will be recorded at screening.

Subjects will undergo a full physical examination at screening, including recording of weight, height, vital signs, 12-lead ECG, echocardiography/MUGA, and determination of ECOG performance status.

Safety laboratory tests, including hematology, coagulation, serum chemistry, and urinalysis, must be completed within 7 days pre-dose. Total triiodothyronine (TT3), free T3 (FT3), free thyroxine (FT4), and thyroid stimulating hormone (TSH) will also be evaluated at screening. All subjects should be tested for hepatitis B virus, hepatitis C virus, and human immunodeficiency virus (HIV).

Women of childbearing potential at screening should have a serum  $\beta$ -chorionic gonadotropin test within 7 days prior to study drug administration unless the age-related spontaneous menopause for  $\geq 12$  consecutive months and follicular estrogen (FSH) increase  $> 40$  mIU/ml, surgical sterilization, or sexual abstinence. Women of non-childbearing potential can be waived from pregnancy tests. If confirmation of menopausal status is required, FSH may be measured at screening.

Oncology (Section 7.2.2), HER2 status, and biomarker evaluation (Section 7.2.6) will also be performed at screening.

In the event of screening failure due to abnormal laboratory tests, a repeat laboratory test is allowed upon agreement between the investigator and the Medical Monitor. Failure of a subject to reach the eligibility criteria at screening will result in screening failure and inability to receive study medication. For subjects who fail screening, the following information needs to be recorded on the eCRF:

- Informed Consent Page;
- Reason for screening failure;
- Demographic information;

- Adverse event;
- Inclusion/Exclusion Criteria Page.

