| Urinalysis                                                               | X     | Every 12 weeks, or as clinically indicated                                                            |  |  |  |  |  | X   | (X)  |     |                            |  |
| Thyroid function                                                                     | X                 | Every 6 weeks, or as clinically indicated                                                             |  |  |  |  |  | X   | (X)  |     |                            |  |
| LVEF                                                                                 | X                 | Every 9 weeks, or as clinically indicated                                                             |  |  |  |  |  | X   |                  | X   | Every 3 months till 1 year |  |
| Troponin                                                                             | X                 | If clinically indicated                                                                               |  |  |  |  |  |     |                  |     |                            |  |
| IL-6                                                                                 |                   | If clinically indicated                                                                               |  |  |  |  |  |     |                  |     |                            |  |
| Serum pregnancy test (if applicable)                                                 | (X)  |                                                                                                       |  |  |  |  |  | (X) |                  |     |                            |  |
| Urine pregnancy test (if applicable)                                                 |                   | (Every 12 weeks)                                                                                      |  |  |  |  |  |     |                  |     |                            |  |
| Follicle-stimulating hormone (only if confirmation of menopausal status is required) | (X)               |                                                                                                       |  |  |  |  |  |     |                  |     |                            |  |

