## 5 STUDY POPULATION

Subjects who meet all the inclusion criteria and none of the exclusion criteria are eligible to be enrolled in this study. Before any study evaluation beyond the subject's routine medical care, the investigators should ensure that the subject or subject's legal representative has provided the written informed consent.

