- I12. Expected survival time  $\geq 3$  months;
- I13. Female subjects of childbearing potential or male subjects with a partner of childbearing potential agree to use highly effective contraception (see Appendix 3) from 7 days before the first dose until 24 weeks after drug withdrawal. Female subjects of childbearing potential must have a negative serum pregnancy test within 7 days before the first dose;
- I14. Subjects are able and willing to comply with protocol-scheduled visits, treatment regimens, laboratory tests, and other study-related procedures.

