E14. Toxicities of prior anti-tumor therapy did not recover to  $\leq$  CTCAE Grade 1 (NCI-CTCAE v5.0) or baseline, with the exception of alopecia and skin pigmentation (any grade);

E15. Prior history of allogeneic bone marrow or organ transplantation;

E16. Prior history of allergic reaction, hypersensitivity reaction, and intolerance to antibody drugs; history of significant allergy to drugs (e.g., severe allergic reactions, immune-mediated hepatotoxicity, immune-mediated thrombocytopenia or anemia);

E17. Pregnant and/or lactating women;

E18. Other conditions that, in the opinion of the investigator, would affect the safety or compliance with the study treatment, including but not limited to moderate to large pleural/ascites/pericardial effusion, refractory pleural/ascites/pericardial effusion, intestinal obstruction or subacute intestinal obstruction, psychiatric disorders, etc.;

E19. BMI  $<$  18.5 kg/m^2 or weight loss  $\geq$  10% within 2 months prior to screening (and the effect of large pleural and ascites on body weight needs to be considered).

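### Section 7.1.1 waives the pre-dose serum pregnancy test for women of childbearing potential who report sexual abstinence, which contradicts inclusion criterion I13

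*Protocol*

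**What the plan says.** Protocol section 7.1.1 (Screening Period) opens its pregnancy-test rule with "Women of childbearing potential at screening should have a serum" beta-hCG test. It gives the timing and begins the exceptions with "within 7 days prior to study drug administration unless the age-related spontaneous menopause for". The menopause exception needs at least 12 consecutive months and FSH above 40 mIU/mL. The list then closes, and the next sentence follows, with "surgical sterilization, or sexual abstinence. Women of non-childbearing potential can be waived from pregnancy tests".

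Inclusion criterion I13 (section 5.1) states: "Female subjects of childbearing potential must have a negative serum pregnancy test within 7 days before the first dose". It adds no exception. On contraception, I13 separately requires that subjects "agree to use highly effective contraception (see Appendix 3) from 7 days before the first dose until 24 weeks after drug withdrawal".

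Section 5 makes the criteria binding: "Subjects who meet all the inclusion criteria and none of the exclusion criteria are eligible to be enrolled in this study". Exclusion criterion E17 (section 5.2) rules out "Pregnant and/or lactating women". In Table 1 the test appears only under the label "Serum pregnancy test (if applicable", with no statement of who is exempt.

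**The concern.** Section 7.1.1 and I13 cover the same women, the same test and the same 7 days, but only 7.1.1 lets abstinence replace the test. Abstinence does not change whether a woman can conceive, and because no duration is set, it cannot rule out a conception that came before it.

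What is at stake is safety and eligibility. A site working from 7.1.1 could skip the test, record the reason as abstinence, and give the first dose of KN026 and KN046 to a woman whose status under E17 has not been verified. She would also be an eligibility deviation that the protocol's own wording had caused. The protocol treats pregnancy as serious elsewhere: it is a reason to stop treatment (section 5.3.1) and must be reported to the sponsor within 24 hours (section 8.2.4).

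**Working it through.** The plan gives no figure to reproduce here, so the check is a comparison of texts.

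| Element | I13 (section 5.1) | Section 7.1.1 |
|---|---|---|
| Who | Women of childbearing potential | Women of childbearing potential |
| Test | Serum, must be negative | Serum beta-hCG |
| Window | 7 days before first dose | 7 days before dosing |
| Exceptions | None | Menopause with raised FSH; surgical sterilization; sexual abstinence |

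**Exceptions one by one**

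1. Menopause (at least 12 months, FSH above 40 mIU/mL): the woman is not of childbearing potential, so I13 does not apply to her. No conflict.
2. Surgical sterilization: the same reasoning. No conflict.
3. Sexual abstinence: the woman is still of childbearing potential, so I13 applies in full. I13 requires the test and 7.1.1 waives it. Conflict.

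**Does another provision settle it?**

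- *Table 1, serum row.* It is marked as applying only where applicable, which leaves open whom it applies to.
- *Table 1, footnote 5.* It lists the serum/urine pregnancy test among the safety laboratory tests due before dosing. That supports I13, but it neither defines who is tested nor withdraws the waiver.
- *The contraception duty in I13.* It starts 7 days before the first dose, so it cannot exclude an earlier conception.
- *Appendix 3.* I13 cites it for contraception only. The test sentence in I13 is separate and unqualified, so acceptance of abstinence as a contraceptive method would not waive the test.

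**Illustration of untested exposure** (the finding does not depend on it). Assume that the 12-weekly urine test in Table 1 is counted from the first dose, is applied to this woman, and is done before that visit's infusion.

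- Dosing in Table 1: KN026 at Weeks 1, 2 and 4, then every 3 weeks from Week 7; KN046 at Weeks 1 and 4, then every 3 weeks from Week 7.
- Next routine test: 1 + 12 = Week 13.
- KN026 infusions before Week 13: Weeks 1, 2, 4, 7, 10 = 5.
- KN046 infusions before Week 13: Weeks 1, 4, 7, 10 = 4.

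Table 1 states no starting point for the urine test, and that row too is conditional. If a urine test is done before the Week 1 dose, no infusion is given untested (0 and 0). If the row is judged not to apply to her, no routine on-treatment test is scheduled and the count has no fixed limit.

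**The case against.** The strongest reply is that the protocol already contains the right rule and a safeguard. I13 is unqualified, section 5 makes it binding, and 7.1.1 itself says that a subject who does not reach the eligibility criteria is a screening failure and cannot receive study medication. A site that applies all of this cannot dose the woman untested. On this view an untested first dose needs a site to overlook I13, and the fault is editorial.

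Most of that stands. I13 does govern, and this is why the contradiction is minor. But the screening-failure sentence does not cancel the waiver a few lines above it. It only means that 7.1.1 excuses a woman from a test and then, through I13, makes her ineligible for lack of it.

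A second reply is that the sentence is a garbled definition of women who are not of childbearing potential, since two of its three items describe exactly that. This is plausible, but it does not help. Read that way, abstinent fertile women are classed as unable to conceive, and the next sentence waives pregnancy tests for them generally, which could take in the 12-weekly urine test. Either reading needs the same correction.

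Two limits are fair. Appendix 3 is not in the text available here, so whether it defines childbearing potential is unknown. And the illustration's range is so wide that 5 and 4 infusions should not be taken as an estimate.

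**Conclusion.** The concern holds. Section 7.1.1 states an exemption that I13 does not allow, and no other provision seen here removes it. It is a minor internal contradiction, because I13 controls eligibility, but it sits in the working instruction for screening and bears on the check that enforces E17.

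How many women it could affect cannot be derived from the protocol, and no number is claimed. There is no effect on ORR, DOR, their confidence intervals or the planned cohort sizes. The conclusion rests on one premise beyond the text: abstinence of unstated length neither removes childbearing potential nor excludes an existing pregnancy.

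**What to change.** Replace the pregnancy-test wording in section 7.1.1 with:

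> All women of childbearing potential must have a negative serum beta-hCG test within 7 days before the first dose. Women who are postmenopausal (at least 12 consecutive months and FSH > 40 mIU/mL) or surgically sterilized are not of childbearing potential and need no pregnancy test.

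This removes abstinence as an exemption, keeps the two valid ones, and brings 7.1.1 into line with I13. When making the change, the sponsor should confirm that Appendix 3 does not define childbearing potential differently.

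The cost is one reworded passage at the next amendment and at most a few extra serum tests, with no change to sample size or analysis.

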### **Treatment Period**

The treatment period begins from Cycle 1 Day 1 of KN046 and KN026 administration and continues until disease progression (see Sections 6.1.3 and 7.2.2.3), significant clinical deterioration (clinical progression), unacceptable toxicity, the subject withdrawal from the study or study treatment, or end of study (see Sections 5.3.1 and 5.3.2).

After disease progression per RECIST 1.1 (Solid Tumors) criteria, if the subject is clinically stable and can benefit from continuing KN026 and KN046 treatment as judged by the investigator, the subject is allowed to continue treatment with KN026 and KN046 (see Section 6.1.3). In this case, subjects may be treated with reference to the iRECIST (solid tumors) criteria (Appendix 2). If treatment with KN046 and KN026 is continued after the progression is confirmed per RECIST 1.1 criteria, KN046 and KN026 should be discontinued immediately once the subject is intolerant of the study drug or experiences treatment failure (see Sections 6.1.3, 5.3.1, and 5.3.2).

During the treatment period, subjects will have visits as specified in the protocol. The window for the visit period is up to 3 days ( $\pm 3$  days) before or after the scheduled visit day (except for the PK and ADA sampling visits required in Table 2).

The evaluations performed during the treatment period are detailed in and should follow the provisions of Tables 1 and 2.

### **End of Treatment Visit (EOT)**

Subjects who discontinue treatment with KN046 and KN026 for any reason must have an EOT visit. The EOT visit should be performed within 7 days of the decision to discontinue treatment, but before starting a new anti-tumor therapy, if applicable, whichever occurs first. The EOT visit may also be performed on the day of the decision to discontinue treatment with KN046 and KN026; if it is within 7 days after the last pre-treatment evaluation, the same tests as those of EOT visit need not be repeated.

The eCRF page for EOT visit must include the date of the decision to discontinue KN046 and KN026 treatment, the date of the last KN046 and KN026 treatment, and any of the following reasons:

- Adverse event;
- Abnormal laboratory value(s);
- Abnormal operation results;
- Protocol deviations;

- Withdrawal of informed consent;
- Lost to follow-up;
- Death (must be noted it is caused by "study indication" or "other" reasons);
- Disease progression as per RECIST 1.1 criteria;
- End of treatment according to the protocol requirements;
- Other causes, including clinical progression, administrative problems.

If no PD as defined by RECIST 1.1 occurs at the EOT visit, subjects will be asked to continue tumor evaluations. If a subject withdraws the ICF, it must be clearly stated that if he/she is willing to continue the follow-up after the end of treatment (see Sections 5.3.2, 7.1.4, 7.1.5).

See Table 1 for the specific assessments at the EOT visit.

### **30-Day and 90-Day Safety Visits**

A safety follow-up visit is required for subjects 30 days ( $\pm 3$  days) after the last dose of KN026 and/or KN046 and 90 days ( $\pm 7$  days) after the last dose of KN046. For subjects who discontinue KN046 treatment first and continue to receive KN026, the 90-day safety follow-up visit is not required if 30 days after the last dose of KN026 are later than 90 days after the last dose of KN046.

After the EOT visit, AEs need to be recorded up to 30 days after the last dose of study drug. Thereafter, all SAEs and treatment-related non-serious AEs (including irAEs) will be recorded until 90 days after the last dose of KN046. SAEs that persist after the 30-day or 90-day safety follow-up visit are required to be monitored by the investigator until stabilization or until the outcome is known.

Subsequent anti-tumor therapies, tumor imaging evaluations (see Section 7.2.2, if applicable), etc. will also be collected during the safety follow-up period. Please refer to Table 1 for the contents of visits during the safety follow-up period.

### **Long-term Follow-up**

Serious adverse events (SAEs) that continue beyond the 90-day safety follow-up visit will need to be monitored in the long-term follow-up until stabilization or until the outcome is known, unless the subject is documented as "lost to follow-up". The KN046 and/or KN026 treatment-related SAEs should be recorded, regardless of the time of occurrence or the time from discontinuation of KN046 or KN026, and reported to the regulatory authorities in accordance with local regulatory requirements.

The survival status information and subsequent anti-tumor therapy will be collected every 12 weeks ( $\pm 14$  days) after the decision to discontinue treatment, regardless of whether or not the subject has an EOT visit. Survival follow-up will continue until 1 year after the last subject

completes KN026 and/or KN046 treatment; the completion of the last study-related telephone contact or visit, withdrawal from the study or lost to follow-up (i.e., the investigator is unable to contact the subject) of the last subject; death or premature withdrawal from the study of all subjects; or the sponsor assesses that the study has met the study expectations (e.g., completion of the primary endpoint assessments) (Section 4.1.1).

Subjects who have no PD as defined by RECIST 1.1 after the EOT visit will be asked to continue tumor evaluations (Section 7.2.2.3).

The evaluations to be completed during the long-term follow-up period are detailed in Table 1.

### **End of Study**

The end of the study is defined as 1 year after the last dose of all subjects; the completion of the last study-related telephone contact or visit, withdrawal from the study or lost to follow-up (i.e., the investigator is unable to contact the subject) of the last subject; death or premature withdrawal from the study of all subjects; or the sponsor assesses that the study has met the study expectations (e.g., completion of the primary endpoint assessments), whichever occurs first.

Note: If the sponsor concludes that the study has met the expectations, but there are still patients on treatment, the sponsor will provide a subsequent protocol to continue providing KN046 and/or KN026 and certain safety follow-up visit for the patients.

## **STUDY EVALUATIONS**

### **Demographics and Other Baseline Characteristics**

The study evaluations described in this section must be completed at screening.

#### ***Demographic Data***

The following data are collected during the screening period:

- Date of birth;
- Sex;
- Race;
- Ethnicity.

#### ***Tumor Diagnosis***

Tumor disease information for each subject needs to be confirmed and documented at screening, including:

Version No.: 4.2

- The detailed tumor history, including histopathological type, grade and stage, determined according to the criteria for tumors, lymph nodes, and metastasis classification from the Union for International Cancer Control (UICC) at the time of diagnosis;
- All prior anti-tumor therapies (including surgery, radiotherapy and chemotherapy, immunotherapy);
- Any other disease receiving chemotherapy, radiotherapy, or immunotherapy;
- Current tumor symptoms and signs, and adverse reactions to current and/or prior anti-tumor therapies;
- Current tumor status.

